|                           | 
Cohort 2: Patients randomized to IBI362 or placebo initiate treatment with 1.5 mg once-weekly with dose escalations every 4 weeks by 1.5 mg until the maintenance dose (4.5 mg) will be achieved.
 
If 3.0 mg or 4.5 mg is not tolerated in Cohort 2, the dose should be adjusted according to the criteria in Table 1.
 
Cohort 3: Dosing should not be started until the patients in Cohort 2 complete the 4-week tolerability evaluation of 1.5 mg. If 1.5 mg is not well-tolerated, 2.0 mg and higher doses in Cohort 3 will not be explored. Patients randomized to IBI362 or placebo initiate treatment with 2.0 mg once-weekly with dose escalations every 4 weeks by 2.0 mg until the maintenance dose (6.0 mg) will be achieved.
 
The study will consist of a 3-week screening period, a 12-week double-blind treatment period, and an 8-week follow-up period.
 
Discontinuation Criteria: If any of the following criteria are met, the investigator and the sponsor should immediately initiate a discussion to decide whether to terminate dose escalation.
 
 
• Occurrence of at least one serious treatment-emergent adverse event related to IBI362 (except for expected adverse events related to the pharmacological properties of IBI362, such as hypoglycemia, etc.).
 
• No less than 4 patients experience symptomatic hypoglycemic events (plasma glucose levels < 3.0 mmol/L) at a specific dose level, and those events are considered to be related to IBI362.
 
• No less than 2 patients receiving IBI362 experience persistent (more than one week) symptoms of acute pancreatitis.
 
• No less than 2 patients experience severe IBI362-related, non-serious adverse events at the same dose, regardless of whether the event is associated with the same organ or system.
 
 |

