**Table 1. Dose adjustment reference table in escalation process**

| Weeks                 |                | 1         | 2   | 3   | 4   | 5         | 6            | 7       | 8       | 9         | 10           | 11      | 12      |        |    |    |    |
|-----------------------|----------------|-----------|-----|-----|-----|-----------|--------------|---------|---------|-----------|--------------|---------|---------|--------|----|----|----|
| Cohort 1 (N = 12)     | IBI362/Placebo | 1.0 mg QW |     |     |     | 2.0 mg QW |              |         |         | 3.0 mg QW |              |         |         |        |    |    |    |
|                       | Dulaglutide    | 1.5 mg QW |     |     |     |           |              |         |         |           |              |         |         |        |    |    |    |
| Weeks                 |                | 1         | 2   | 3   | 4   | 5         | 6            | 7       | 8       | 9         | 10           | 11      | 12      |        |    |    |    |
| Cohort 2 (N = 12)     | IBI362/Placebo | 1.5 mg QW |     |     |     | 3 mg QW   |              |         |         | 4.5 mg QW |              |         |         |        |    |    |    |
|                       | Dulaglutide    | 1.5 mg QW |     |     |     |           |              |         |         |           |              |         |         |        |    |    |    |
| Weeks                 |                | 1         | 2   | 3   | 4   | 5         | 6            | 7       | 8       | 9         | 10           | 11      | 12      |        |    |    |    |
| Cohort 2 (backup 1) * | IBI362/Placebo | 1.5 mg QW |     |     |     | 3 mg      | Discontinued | 2.25 mg | 2.25 mg | 3 mg QW   |              |         |         |        |    |    |    |
| Weeks                 |                | 1         | 2   | 3   | 4   | 5         | 6            | 7       | 8       | 9         | 10           | 11      | 12      |        |    |    |    |
| Cohort 2 (backup 2) # | IBI362/Placebo | 1.5 mg QW |     |     |     | 3 mg QW   |              |         |         | 4.5 mg    | Discontinued | 3.75 mg | 3.75 mg |        |    |    |    |
| Weeks                 |                | - 4       | - 3 | - 2 | - 1 | 1         | 2            | 3       | 4       | 5         | 6            | 7       | 8       | 9      | 10 | 11 | 12 |

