**Notes:**

\* If patients in Cohort 2 cannot tolerate 3.0 mg during dose escalation, the dose should be reduced to 2.25 mg after 1-week break in Cohort 2 (backup1), and subsequent dose escalation should be performed as Cohort 2 (backup1);

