# If patients in Cohort 2 cannot tolerate 4.5 mg during the escalation, the dose should be discontinued for 1 week and reduced to 3.75 mg in Cohort 2 (backup2), and the dose should be maintained until the end of the trial;

& Patients in Cohort 3 should not start until patients in Cohort 2 complete the 4-week tolerance study at 1.5 mg. If patients in Cohort 2 cannot tolerate 1.5 mg, patients in Cohort 3 will not explore 2.0 mg or higher.

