## 3.2 Phase 1b/2 Study Design

### 3.2.1 Overall Study Design

The study will be planned to include 42 patients with type 2 diabetes who failed to control HbA1c after at least 2 months of lifestyle intervention or stable dose of metformin ( $\geq 1000$  mg/day or maximum tolerated dose). The study will be divided into three cohorts, which will be Cohort 1 (n = 14), Cohort 2 (n = 14) and Cohort 3 (n = 14). Patients in each cohort will be randomized 8:4:2 to IBI362 group (n = 8), placebo group (n = 4), or dulaglutide 1.5 mg group (n = 2). The active control, dulaglutide, will be administered as 1.5 mg once-weekly for 12 weeks in Cohorts 1, 2 and 3, and the dosing schedules for IBI362 and placebo are described below:

**Cohort 1:** Patients randomized to IBI362 or placebo initiate treatment with 1.0 mg once-weekly with dose escalations every 4 weeks by 1 mg until the maintenance dose (3.0 mg) will be achieved.

**Cohort 2:** Patients randomized to IBI362 or placebo initiate treatment with 1.5 mg once-weekly with dose escalations every 4 weeks by 1.5 mg until the maintenance dose (4.5 mg) will be achieved.

If the patient failed tolerate 3.0 mg or 4.5 mg with the met discontinuation criteria, the patient needs to explore the next dose according to Cohort 2 (backup 1) or Cohort 2 (backup 2).

**Cohort 2 (backup 1):** With the tolerated dose of 3.0 mg, the dose should be reduced to 2.25 mg after 1-week break and treat with it for 2 weeks. After that, if it is well-tolerated, the dose will be increased to 3.0 mg and treat for 4 weeks.

**Cohort 2 (backup 2):** If the dose of 4.5 mg is intolerable to the patient, the dose should be reduced to 3.75 mg after 1-week break and administered continuously for 2 weeks till the end of the trial.

**Cohort 3:** Dosing should not be started until the patients in Cohort 2 complete the 4-week tolerability evaluation of 1.5 mg. If 1.5 mg is not well-tolerated, 2.0 mg and higher doses in Cohort 3 will not be explored. Patients randomized to IBI362 or placebo initiate treatment with 2.0 mg once-weekly with dose escalations every 4 weeks by 2.0 mg until the maintenance dose (6.0 mg) will be achieved.

The study will consist of a 3-week screening period, a 12-week double-blind treatment period, and an 8-week follow-up period.

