- 2) The investigator may terminate or withdraw a subject from the study because of AEs. (Considering that gastrointestinal adverse reactions may be related to the efficacy, it is recommended that the investigator may consider to adjust the titration rate at first. Only if the severe adverse events continues after adjustment, the investigator will terminate the patient because of intolerance);
- 3) Patients with poor compliance who do not receive medication or test before completing the whole trial and cannot insist on completing the trial as planned, including patients who cannot do a good job in diet control, do not take medicine as required, or have other conditions that may affect the efficacy evaluation;
- 4) Withdrawal of consent by the patient;
- 5) Patients with blindness due to various reasons;
- 6) Female patient becomes pregnant;
- 7) The investigator considers it inappropriate to continue to participate in the trial.

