#### 8.6.3 Contents of adverse event records

The investigator should completely record any AE, including diagnosis (if no diagnosis, record the symptoms and signs including laboratory abnormalities), start and stop time (if applicable), severity and changes, whether it is an SAE, actions taken for the study drug, treatment given due to AE and the outcome of the event, and the relationship between the AE and the study drug.

For serious adverse events, the investigator provided the date on which the AE met the criteria for an SAE, the date that the investigator became aware of the SAE, the rationale for determining the AE as an SAE, the date of hospitalization, the date of discharge, the possible cause of death, the date of death, whether an autopsy will be performed, the assessment of causality with the study procedures, the assessment of causality with other drugs, and other possible causes of the SAE. The investigator should provide the basis for judging the correlation and the description of SAE. The description of an SAE should also include the patient's number, age, gender, height and weight; the patient's indications for the investigational drug treatment, disease stage and relevant general conditions; the clinical course of the SAE including its occurrence, development, outcome and results; laboratory test results related to the SAE (the test time, unit and normal range must be provided); past history related to the SAE, concomitant diseases and their occurrence and duration; medication history related to the SAE, concomitant drugs and their start, duration, dosage and administration; and details about the start, duration, dosage and administration of the investigational drug treatment.

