### **6.6.1 Adverse events**

Classified by date of event:

- Pre-treatment Adverse Events: Adverse events that occurred from signing of informed consent until the first dose of study treatment.
- Treatment-emergent adverse events (TEAEs): Adverse events that occurred or became serious during the first dose of study treatment through 56 days after last dose.
- Post-treatment adverse events: Adverse events that occurred or became serious after 56 days following the last dose until the end of the trial.

If the AE start date is completely/partially missing, impute the date according to Section 5.3 before assigning pre-treatment/on-treatment/post-treatment adverse events.

The incidence (frequency) of all AEs, TEAEs, severe TEAEs, TEAEs leading to permanent treatment discontinuation, drug-related TEAEs (TRAEs), severe TRAEs, TRAEs leading to permanent treatment discontinuation, AESIs, severe AESIs, AESIs leading to permanent treatment discontinuation, SAEs, SAEs related to study drug, and SAEs leading to permanent treatment discontinuation will be summarized by treatment group.

The following categories of adverse events will be summarized by SOC, PT, and SOC, PT, and severity from MedDRA coding:

- TEAEs
- TEAE leading to permanent discontinuation
- TRAE
- TRAEs leading to permanent discontinuation
- AESI
- AESIs leading to permanent discontinuation
- For gastrointestinal reactions, the number of events with gastrointestinal reactions was also provided. Gastrointestinal reactions including adverse reactions with preferred terms of nausea, vomiting, diarrhea, dyspepsia, abdominal distension, abdominal discomfort, and gastroesophageal distress

TEAEs will also be summarized by PT in MedDRA and the number of events of TEAEs will be calculated.

Treatment-emergent SAEs, treatment-emergent SAEs related to study drug, and treatment-emergent SAEs leading to permanent discontinuation will be summarized by SOC and PT.

Hypoglycemic events will be summarized by treatment group.

The above summary tables are sorted according to the incidence of AEs in all subjects who received IBI362.

Subjects who discontinued treatment due to AEs, subjects who experienced SAEs, and subjects who died will be listed (at least include AE start date, end date, severity, relationship with drug, action taken, and outcome). All AEs will be listed.

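### SAP 6.6.1 counts dose-affecting adverse events only as permanent discontinuation, so a completed step-down, which has a written schedule only in Cohort 2, appears in no action-based table

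*Combined protocol and SAP*

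**What the plan says.** **What is tabulated.** SAP 6.6.1 summarises, by treatment group, all TEAEs, TRAEs, AESIs and SAEs, with severity. The only rows defined by what happened to study drug are those for permanent discontinuation, for example "TEAEs leading to permanent treatment discontinuation, drug-related TEAEs (TRAEs), severe TRAEs, TRAEs leading to permanent treatment discontinuation". No row covers interruption, dose reduction or delayed escalation. No table counts patients who meet the single-patient intolerance criteria that follow protocol Table 1.

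**What is done on intolerance in Cohort 2.** The Synopsis states: "If 3.0 mg or 4.5 mg is not tolerated in Cohort 2, the dose should be adjusted according to the criteria in Table 1". Table 1 has two backup schedules, labelled as in "Cohort 2 (backup 1) * | IBI362/Placebo", so they cover placebo patients too. Backup 1 is one dose of 3.0 mg, a week off, two doses of 2.25 mg, then four of 3.0 mg. For backup 2, protocol 3.2.1 says "the dose should be reduced to 3.75 mg after 1-week break and administered continuously for 2 weeks till the end of the trial". SAP 2.2 repeats both.

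**What is done elsewhere.** For Cohorts 1 and 3, SAP 2.2 makes each increase conditional on good tolerance and does not say what follows otherwise. Dulaglutide is a fixed 1.5 mg with no backup row. Three statements are not limited to a cohort:
- A note to Table 2 says dose is adjusted to tolerance throughout treatment, but refers to the adjustment table, whose backup rows are for Cohort 2 only.
- Note 4 to Table 3 calls for adjustment at the investigator's discretion when the tolerance criteria are met.
- Protocol 4.4.2, on gastrointestinal reactions, says "it is recommended that the investigator may consider to adjust the titration rate at first".

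**What is recorded.** Protocol 8.6.3 requires each AE record to include "actions taken for the study drug".

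**The concern.** Safety and tolerability are the primary objective. A reader will naturally use AEs leading to discontinuation as a summary of tolerability. In Cohort 2 a patient who could not stay on the assigned schedule has a written route that avoids this count. In the other IBI362 cohorts any such route is discretionary, and in the dulaglutide arm there is no titration to adjust. The same degree of intolerance could therefore yield different permanent-discontinuation counts for reasons of schedule rather than drug. The planned summaries would also not say, for any arm, how many patients had to change dosing because of an adverse event.

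**Working it through.** **1. Plan figure.** Enrolment is 3 × (8 + 4 + 2) = 42, as stated in protocol 9.2. There is no power calculation to reproduce.

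**2. Do the other planned outputs show a completed step-down?** Doses are summed from Table 1.
- Cohort 2 as assigned: 4 × 1.5 + 4 × 3.0 + 4 × 4.5 = 36 mg.
- Backup 1: 4 × 1.5 + 3.0 + 0 + 2 × 2.25 + 4 × 3.0 = 25.5 mg.
- Backup 2: 4 × 1.5 + 4 × 3.0 + 4.5 + 0 + 2 × 3.75 = 30 mg.

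*Disposition (SAP 6.2).* Premature discontinuation means missing the last scheduled dose. A patient who finishes a backup schedule is not counted.

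*Exposure weeks (SAP 6.4.1).* The formula runs from first to last dose plus 7 days: (78 − 1 + 7)/7 = 12.0 under both backups, the same as a full course. The week off is invisible.

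*Relative dose intensity (SAP 6.4.1).* Against the assigned schedule it is 25.5/36 = 70.8% or 30/36 = 83.3%, which shows the reduction. If planned dose is read as the backup schedule, it is 100% in both cases. The SAP wording does not settle which. Neither reading gives the reason for the reduction.

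*Listings (SAP 6.6.1).* All AEs are listed, but action taken is a specified column only for patients who discontinued because of an AE, had an SAE or died.

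**3. How far can the permanent-discontinuation rows move?** Let p be the probability that a patient does not tolerate an escalated dose, and r the share of such Cohort 2 patients whom the step-down keeps on drug. Neither is in the documents, so both are assumed. The same p is used in every arm, and every intolerant patient in Cohorts 1 and 3 is taken to stop. Expected counts of 8 are 8p in Cohort 1 or 3 and 8p(1 − r) in Cohort 2.

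| p | Cohort 1 or 3 | Cohort 2, r = 0 | r = 50% | r = 80% | r = 100% |
|---|---|---|---|---|---|
| 10% | 0.8 | 0.8 | 0.4 | 0.16 | 0 |
| 25% | 2.0 | 2.0 | 1.0 | 0.4 | 0 |
| 40% | 3.2 | 3.2 | 1.6 | 0.64 | 0 |

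At r = 80%, the chance that the row shows at least one patient of 8 is 1 − (1 − p)^8 in Cohort 1 or 3, and 1 − (1 − 0.2p)^8 in Cohort 2. That gives 0.57 against 0.15 at p = 10%, 0.90 against 0.34 at 25%, and 0.98 against 0.49 at 40%.

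Placebo is pooled across cohorts (SAP 6.1), so 4 of its 12 patients are under the Cohort 2 rule. With the same p = 25% and r = 80%, its expected count is 8 × 0.25 + 4 × 0.25 × 0.2 = 2.2 of 12, or 18.3%.

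**4. What if Cohorts 1 and 3 also adjust?** Let s be the share kept on drug there by discretionary adjustment. The gap from Cohort 2 becomes 8p(1 − s) − 8p(1 − r) = 8p(r − s). At p = 25% and r = 80% it is 8 × 0.25 × 0.8 = 1.6 patients if s = 0, 0.6 if s = 50%, nil if s = 80%, and −0.4 if s = 100%. Direction as well as size therefore depends on unknowns.

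**5. After the fix.** A row for any change of study drug has expectation 8p in every IBI362 arm (0.8, 2.0 or 3.2), whatever r and s are.

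**The case against.** The strongest reply is that nothing is hidden. An event that leads to a step-down still enters the TEAE, TRAE and severity tables where it qualifies. The single-patient intolerance criteria concern hypoglycaemia and severe drug-related intolerance, and protocol 8.3 makes hypoglycaemia, gastrointestinal reactions and severe related non-serious events AESIs. SAP 6.6.1 adds hypoglycaemia summaries and gastrointestinal event counts. In the reported table of all TEAEs, the 4.5 mg arm has the highest any-TEAE count (8 of 8) and the most patients with gastrointestinal disorders (5 of 8), so the general tables did not flatter Cohort 2. All of this stands, although it does not test the discontinuation rows.

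A reader might infer more than the documents support, in three ways:
- *That intolerance vanishes in Cohort 2 but is counted elsewhere.* It is missing only as an action-based harm. A Cohort 2 patient who stops despite the step-down still counts, and intolerance of 1.5 mg has no step-down. No passage says that intolerance in Cohort 1 or 3 means a permanent stop, and three statements allow adjustment outside Cohort 2.
- *That the maximum tolerated dose is biased.* It follows from the stopping criteria in protocol 3.2.3, which count related SAEs, symptomatic hypoglycaemia, persistent pancreatitis symptoms and severe related non-serious events. None uses permanent discontinuation.
- *That there is a spurious 25-point gap between cohorts.* At p = 25% this requires every intolerant patient in Cohorts 1 and 3 to stop and none in Cohort 2. It is one corner of the range.

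It is also fair to say that SAP 6.1 plans description and, as a rule, no comparison between arms. That argues against making a new row a formal comparison. It does not argue against reporting one.

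**Conclusion.** The point holds as a reporting gap. The plan's only dosing-related measure of AE harm is permanent discontinuation, only Cohort 2 has a written break and reduction, and no other planned summary reliably shows a completed step-down or links it to an adverse event. Permanent-discontinuation rates can understate intolerance in any arm where dosing is adjusted, most clearly in Cohort 2, and should not be read as like-for-like. In the illustration at p = 25%, the understatement in Cohort 2 ranges from none to 2 patients of 8. The difference from Cohorts 1 and 3 could also be nil or reversed if those cohorts adjust as often or more often. These figures rest on assumed p, r and s and on equal intolerance across arms. The documents do not establish a direction for the actual data.

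**What to change.** 1. In SAP 6.6.1 add, by treatment group and for TEAEs, TRAEs and AESIs, the number and percentage of patients with events leading to (a) interruption, (b) dose reduction, (c) delayed or altered titration, (d) permanent discontinuation, and (e) any change of study drug, meaning any of (a) to (d). Keep these rows descriptive.
2. In SAP 6.6.1 state that the listing of all AEs includes action taken.
3. In SAP 6.4.1 define the total planned dose as the originally assigned cohort schedule (36 mg for IBI362 in Cohort 2), not a backup schedule.
4. The sponsor should reconcile the general dose-adjustment statements (the Table 2 note, Table 3 note 4 and protocol 4.4.2) with the Cohort 2-only backup rows in Table 1, so that the rows above have a clear meaning in each arm. No dosing rule is proposed here.

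The cost is a few table rows and two or three SAP sentences. The action-taken data are already required by protocol 8.6.3, so no new collection is needed.

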## 7 STUDY ASSESSMENTS

### 7.1 Safety and Tolerability Assessments Metrics

- **Safety and tolerability:** During dose escalation, the incidence and severity of various adverse events at different dose stages will be recorded. The main complaints of patients, physical examination, laboratory tests (blood routine, blood biochemistry, blood lipid, coagulation function, urine routine, myocardial enzyme spectrum, serum amylase and/or lipase, thyroid function, calcitonin, etc.), vital signs (pulse, respiration, blood pressure, body temperature), 12-lead ECG and other examinations; medication compliance analysis will be performed to determine the correlation with the study drug and record the name, clinical characteristics, severity, occurrence and end time, treatment methods and outcomes of adverse events, correlation with the study drug and other information;
- **Maximum tolerated dose:** If the dose exploration is stopped when the criteria for stopping dose escalation are met at a certain dose level, the previous dose is the maximum tolerated dose. If the criteria are still not met when the maximum exploratory dose is reached, the maximum tolerated dose is greater than or equal to the maximum escalation dose;

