## 8. safety reporting and adverse event management

### 8.1 Definition of Adverse Events

An adverse event (AE) is defined as any untoward medical occurrence, whether or not there is a causal relationship with the study drug, in a clinical study subject from the time informed consent form is signed through 90 days after the last dose of study drug, and includes, but is not limited to, the following:

- Exacerbation of pre-existing (prior to clinical study) medical conditions/diseases (including worsening of symptoms, signs, laboratory abnormalities);

- Any newly developed adverse medical conditions (including symptoms, signs and newly diagnosed diseases);
- Clinically significant abnormal laboratory values or results.

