### **3 Endpoints**

#### **3.1 SAFETY, TOLERABILITY AND MAXIMUM TOLERATED DOSE EVALUATION**

- Safety and tolerability: During dose escalation, the incidence and severity of adverse events at each dose level, including chief complaint, physical examination, laboratory tests (hematology, blood chemistry, lipid panel, coagulation function, urinalysis, myocardial enzymes, serum amylase and/or lipase, thyroid function, calcitonin, etc.), vital signs (pulse, respiration, blood pressure, body temperature), 12-lead ECG and other examinations; treatment compliance; and record the name, clinical characteristics, severity, start and stop time, supportive care and outcomes of adverse events, correlation with the study drugs;
- Maximum tolerated dose: If the dose exploration is stopped when the criteria for stopping dose escalation are met at a certain dose level, the previous dose is the maximum tolerated dose. If the criteria are still not met when the maximum exploratory dose is reached, the maximum tolerated dose is greater than or equal to the maximum escalation dose.

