## **6 Statistical Analysis Methods**

### **6.1 GENERAL PRINCIPLES**

All statistical analyses will be performed using SAS 9.4 (or later version). This trial is mainly based on descriptive statistics, and in principle, no comparison will be made.

All data collected in this study will be presented in data listings and summarized in tables by treatment group, unless otherwise specified. Subjects receiving placebo in different cohorts will be combined and analyzed in summary tables.

Categorical data were presented as frequency (percentage). Unless otherwise specified, the number of subjects in each treatment group in the corresponding study population will be the denominator for the percentages. Percentages will be displayed to 1 decimal place.

Continuous data will be shown as mean  $\pm$  standard deviation or median (minimum, maximum). The mean and median will be displayed to 1 more decimal place than the original data, the standard deviation will be displayed to 2 more decimal places than the original data, and the maximum and minimum values will be displayed to the same decimal place as the original data. For PK parameters, geometric means and coefficients of variation will be displayed to the first decimal place, unless otherwise specified.

Baseline value: defined as the last available measurement prior to receiving the first dose of study treatment.

The following notation will be used in the tables of statistical analysis:

| Treatment Group in Protocol                                   | Treatment Groups in Statistical Analysis |
|----------------------------------------------------------------------|-------------------------------------------------|
| Cohort 1, treated with IBI362                                 | IBI362 – Cohort 1                               |
| Cohort 2, treated with IBI362                                 | IBI362 – Cohort 2                               |
| Cohort 3, treated with IBI362                                 | IBI362 – Cohort 3                               |
| Cohort 1, Cohort 2, Cohort 3, Placebo Treated                 | Placebo                                         |
| Cohort 1, Cohort 2, Cohort 3, treated with dulaglutide 1.5 mg | Dulaglutide 1.5 mg                              |

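### The primary endpoint is adverse events at each dose level, but the SAP tabulates them only by cohort, and each IBI362 patient is planned to take three doses

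*Combined protocol and SAP*

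**What the plan says.** **Endpoint.** SAP 3.1 gives the safety endpoint as "During dose escalation, the incidence and severity of adverse events at each dose level"; protocol 2.2.1 has the same wording. Protocol 7.1 restates it: "the incidence and severity of various adverse events at different dose stages will be recorded". The maximum tolerated dose (MTD) is also defined by dose: if the stopping criteria are met at a level, "the previous dose is the maximum tolerated dose".

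**Dosing.** Each IBI362 patient is planned to take three doses, four weeks each: 1.0, 2.0, 3.0 mg in Cohort 1; 1.5, 3.0, 4.5 mg in Cohort 2; 2.0, 4.0, 6.0 mg in Cohort 3 (protocol synopsis).

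**Analysis.** SAP 6.1 sets the default: "All data collected in this study will be presented in data listings and summarized in tables by treatment group, unless otherwise specified". Its notation table then fixes the groups as IBI362 Cohorts 1, 2 and 3, pooled placebo, and dulaglutide. In SAP 6.6.1 the sentence on overall AE incidences ends "SAEs leading to permanent treatment discontinuation will be summarized by treatment group", and hypoglycaemia is summarised in the same way. Treatment-emergent adverse events (TEAEs) are defined as: "Adverse events that occurred or became serious during the first dose of study treatment through 56 days after last dose". The analysis section of the protocol (9.4.3) groups by arm. Neither document specifies an AE table by dose level, dose phase or dose at onset, and the table of changes in SAP 2.5.2 does not record that such an analysis was dropped.

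**The concern.** The endpoint and its planned analysis use different units. The endpoint asks how often, and how severely, events occur at a given dose. The tables answer how often they occur at any time in a cohort that passes through three doses and then an eight-week follow-up. A reader of the final tables could not see whether events cluster at the starting dose, at each step up, or at the target dose. For a dose-escalation study whose stated aim is to find the safe dose range, that is the primary question.

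A smaller point concerns the TEAE definition. Apart from new events, it admits only events that became serious, whereas protocol 8.1 counts as an AE any "Exacerbation of pre-existing (prior to clinical study) medical conditions/diseases (including worsening of symptoms, signs, laboratory abnormalities".

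**Working it through.** **1. The plan's own figures.** Sample size: 3 × (8 + 4 + 2) = 42, as stated. The row for any TEAE in the reported Table S3 reproduces with whole groups as denominators: 6/8 = 75.0%, 8/8 = 100%, 7/8 = 87.5% for the three IBI362 columns; 4/6 = 66.7% for dulaglutide; 9/12 = 75.0% for pooled placebo. Each IBI362 column is therefore a whole cohort. The columns are headed 3.0, 4.5 and 6.0 mg.

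**2. How much of the counted time precedes the target dose.** The inputs are the four-week steps (synopsis), first dose on Day 1, target dose from Day 57 and last dose on Day 78 (protocol Table 2), and the 56-day tail (SAP 6.6.1).
- Doses below target: (4 + 4)/12 = 8/12 = 66.7%.
- TEAE window: 78 + 56 = 134 days.
- Days before the target dose: 56/134 = 41.8%. The other 78 days are Days 57 to 78 (22 days) plus the 56-day tail.

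**3. Whether cohort incidence identifies incidence at a dose.** Let p1, p2, p3 be the risks of a first onset in the three phases. These values are assumed for illustration; the documents give none. Cohort incidence = 1 − (1 − p1)(1 − p2)(1 − p3).
- 20%, 10%, 5%: 1 − 0.80 × 0.90 × 0.95 = 31.6%.
- 5%, 10%, 20%: 1 − 0.95 × 0.90 × 0.80 = 31.6%.
- 10%, 10%, 10%: 1 − 0.90³ = 27.1%.

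The first two patterns give the same column entry, although the target-dose risk differs fourfold.

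**4. An example in the reported table.** Decreased appetite is 4/8 in the column headed 4.5 mg and 2/8 in the column headed 6.0 mg. From the table alone it cannot be seen whether the four patients were taking 1.5, 3.0 or 4.5 mg at onset.

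**5. What a dose-level table would contain.** With full retention and no backup regimen, there are seven planned levels: 1.0, 1.5, 4.0, 4.5 and 6.0 mg with 8 patients each, and 2.0 and 3.0 mg with 16 each (8 from each of two cohorts). The total is 5 × 8 + 2 × 16 = 72 patient-periods = 24 patients × 3. Within cohort, every cell has 8 patients, so the exact 95% upper limit for 0/8 is 1 − 0.025^(1/8) = 36.9%.

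**6. The TEAE wording.** The SAP names events that became serious. Protocol 8.1 names exacerbation, and the note on pre-existing medical conditions in protocol 8.6.3 has worsening in severity, frequency or nature after entry recorded as an AE. The SAP wording is narrower than both. Its abbreviation list also expands SAE as a severe, not a serious, adverse event, so the intended meaning is uncertain.

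**The case against.** **Dose level may simply mean cohort.** The documents do use dose loosely: protocol 5.1.2 and 9.4.1 speak of dose groups, and protocol 3.1.1 describes a study of three dosing regimens. Cohort tables also preserve the randomised comparison with placebo. That part stands, and is a reason to keep those tables. The reading does not fit the endpoint itself, which is set during escalation and restated as dose stages. Nor does it fit the stopping criteria in protocol 3.2.3, two of which count patients at a given dose, or SAP 3.4, which keeps each dose phase for glucose and insulin. Grouping by actual treatment received (SAP 6.6) does not help, because SAP 6.1 fixes the groups as cohorts.

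**The data are there.** All AEs and all exposure are listed, and SAP 5.3 has date-imputation rules for when an event's cycle number must be marked. This stands as far as it goes: the dose at onset can be derived. But a listing is not an incidence estimate, and the cycle-number remark is conditional and feeds no named output.

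**Dose at onset is confounded** with time on drug and with dropout. This is true, and it is why the added tables should be supplementary.

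Stronger conclusions that a reader might draw are not supported:
- *That the SAP credits low-dose events to the target dose.* The SAP's columns are named by cohort. Target-dose headings appear in the reported Table S3.
- *That about two thirds of events would be misattributed.* The 66.7% is a share of doses. Events spread evenly over the TEAE window would put 41.8% before the target dose.
- *That the stopping rules and MTD are disabled.* Under protocol 3.2.3 the criteria are applied during the trial by discussion between investigator and sponsor, and protocol 5.1.2 leaves the sponsor unblinded. They do not wait for the final tables.
- *That a condition which worsens without becoming serious is lost.* Under protocol 8.6.3 the worsening is itself recorded as an AE, so it can count as one that occurred after first dose, and all AEs are listed in any case.
- *That pooling 2.0 mg and 3.0 mg across cohorts simply doubles the information.* Cohort 3 starts at 2.0 mg, while Cohort 1 reaches it after four weeks at 1.0 mg. The 3.0 mg level follows eight weeks of dosing in Cohort 1 and four in Cohort 2. The patients are not clearly exchangeable.

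**Conclusion.** The concern holds. No planned output estimates AE incidence and severity by dose level, which is the primary endpoint, and cohort incidence does not determine it. In every IBI362 cohort, 8 of 12 planned doses and 41.8% of the TEAE window precede the target dose; both figures assume the planned schedule with no dropout and no backup regimen. The share of actual events with onset below the target dose cannot be given from these documents, and the phase risks in the working are illustrative only. The gap is one of tabulation: no data are missing. The heading of Table S3 makes it easier to misread, because a column for a three-step titration carries only the final dose. The TEAE wording is a secondary matter of consistency and adds no weight to the main point.

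**What to change.** Keep the cohort tables. In SAP 6.6.1 add supplementary tables of TEAEs, related TEAEs, severe TEAEs, AEs of special interest and hypoglycaemia by the dose level actually taken at onset (or at worsening), within cohort:
- Use as denominator the patients who received at least one dose at that level.
- Show placebo by the same four-week periods.
- State how events under the backup regimens, and events after the last dose, are assigned to a level.
- Make any pooling of 2.0 mg or 3.0 mg across cohorts secondary, with a note that prior exposure differs.

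Head the cohort columns with the titration regimen, for example 1.0/2.0/3.0 mg, in place of the target dose alone. In the TEAE definition, replace *became serious* with *worsened in severity*, to agree with protocol 8.1 and 8.6.3.

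The cost is SAP wording, one derived variable from existing dosing and AE dates, and a few tables. No new patients, visits or data are needed, and the sample size of 42 is unchanged. The drawback is more tables with small denominators (8 per cell within cohort), in which dose is confounded with time on drug and dropout. They should be read descriptively, with the numbers exposed shown in every column.
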